### Feasibility

The goal is to recruit 146 high-risk and 146 low-risk pregnant participants through invitations sent to the women’s digital mailboxes. However, the possibility of non-response bias and dropout exists due to varying levels of participant inclination or ability to participate. To reduce this potential bias, multiple strategies are implemented, such as reminders, and varied phrasings in the invitation emphasizing the investigation's importance to different degrees. The impact of each strategy may vary depending on population characteristics and recruitment situations [75]. After completion of recruitment, post hoc analysis will be conducted to compare response rates and bias across various sociodemographic groups to determine the extent of any potential non-response bias or dropout in the study. The recruitment process will continue until the target sample size is achieved.

### Compensation to participants

Participants in the intervention, CAU and low-risk control groups receive a gift worth 400 DKK, 200 DKK, and 150 DKK, respectively as an acknowledgement and compensation for their time and effort invested in the project. They receive the gift at the final assessment during pregnancy. If participants choose to withdraw from the study before completion, they receive the gift at their final visit. Participants can get compensated for their time off work (100 DKK/hour) for the outcome assessments if they show documentation of lost income. Transportation costs can be refunded corresponding to the costs of public transportation from the participant’s address of residence to Department of Psychology, Copenhagen. This complies with existing requirements regarding compensation.

### Research ethics

The possible risks related to participating in this study, include experiencing motion sickness in VR, or fatigue due to task repetitions. Further, the affective cognitive tasks are challenging and may be overwhelming to some participants, which could lead to negative self-perceptions regarding task performance and possibly motherhood. We acknowledge such feelings and seek to reduce them by underscoring that the tasks are generally very challenging and that their effort is valuable. In general, the potential risks related to study participation are not associated with persistent harmful consequences for participants’ physical or mental health. In case mothers indicate that they have thoughts of self-harm and experience severe depressive symptoms (with Edinburgh Postnatal Depression Scale (EPDS) ≥ 11 [64, 76]), the named postdoc researcher and psychologist on the project will contact them and, if needed, refer them to psychiatric treatment. Therefore, we consider the potential risks justifiable and the study responsible. Moreover, the potential benefits for the high-risk pregnant women in the active arm are that they may have a lower risk of PPD, and they get support and attention from the psychologist during the study. All participants are followed up after birth and contacted and guided if severe depression symptoms or self-harm arise. The results of the study will have important implications for the scientific understanding of and clinical work with pregnant women at high risk of PPD. Therefore, we argue that the benefits of the study outweigh the potential risks.

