### Procedure

At baseline (T0), all pregnant women undergo a comprehensive (2-h) assessment of affective cognitive processing of infant stimuli and non-emotional cognition, clinical rating of depressive symptoms, and completion of questionnaires regarding attachment to the unborn child, bonding to own parents, emotional relationship with their partner, demographics, clinical history, and state- and trait anxiety (details below). Further, a hair sample is collected from women to assess cortisol levels as a biological measure of stress. Based on the responses on questionnaires and affective cognitive processing, pregnant women are categorised as either at high or low risk of developing PPD (see the “In- and exclusion criteria” section above for specific inclusion criteria for high- and low-risk groups, respectively). High-risk participants are randomized to either PACT or CAU immediately after the baseline testing. Participants in the active intervention group complete a total of five individual training sessions over a period of approximately 5 weeks (for details on the study design, see Fig. 2). Around 5-6 weeks after the baseline assessment, all high-risk pregnant women (in the PACT or CAU arms) undergo their second assessment (T1) of affective cognition and self-ratings, including attachment feelings to the unborn child. For women receiving PACT, this assessment takes place within 1 week after the fifth training session. Lastly, if they have not given birth yet, women in the intervention group are offered a *booster* training session approximately 6-8 weeks after their baseline assessment. If participants face challenges attending in-person sessions, for example due to the late stage of their pregnancy, we will offer to conduct two sessions over the telephone or an online meeting. While computer training will not be feasible in this format, we will emphasize the key points from previous sessions and guide them on how to maintain their progress through home-based exercises like mindfulness techniques.

One week after their due dates, participants receive an e-mail with a link to 5-min online questionnaires regarding the birth, the infant’s health and well-being and mothers’ potential experience of depressive symptoms. On a weekly basis during the first 6 weeks after giving birth, mothers receive links to an online questionnaire to assess their depressive symptoms.

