#### Clinical assessments, interviews, and questionnaires

At baseline T0, participants fill out questionnaires regarding their stress levels, sleep, relation to own parents, unborn child and partner, and depressive symptoms with the State and Trait anxiety questionnaire (STAI-S and T) [58], Pittsburgh Sleep Quality Index [59], Perceived stress [60], Parental Bonding Inventory [61], Maternal Antenatal Attachment Scale [62], Experiences in Close Relationships, Cognitive Emotion Regulation Questionnaire [63] and Edinburgh Postnatal Depression Scale (EPDS) [73, 74]. The EPDS is the internationally most widely used screening tool for PPD and in the Danish population, a cut-off of 11 or higher is the most indicative when screening for PPD [64]. They also rate their experience in VR with the Multimodal Presence Scale [65]. As mentioned previously, participants also fill out the ANRQ [66], which is used to determine their risk status for PPD.

At baseline, participants are interviewed with the HDRS-6 [51, 67], the Standardized Assessment of Personality – Abbreviated Scale (SAPAS) [68] and assessed with the Screen for Cognitive Impairment in Psychiatry (SCIP) [69].

Six months postpartum, mothers undergo an interview utilizing the Present State Examination (PSE), a component of the Schedules for Clinical Assessment in Neuropsychiatry (SCAN) [70], to assess the presence of depressive episodes since childbirth. The clinicians conducting the diagnostic interviews have received specific training and ongoing supervision from the project leader to ensure valid and reliable assessments.

Further, mothers rate their emotions when their child cries with the My Emotions Questionnaire [68]; they fill out the Postpartum Bonding Questionnaire [69] and Parental Stress Scale [70] and evaluate their child’s development with Ages-and Stages Questionnaire: Socio-Emotional (ASQ:SE) [71]; and their reflective functioning is assessed with Parental Reflective Functioning Questionnaire (PRFQ-1) [72].

Mother-infant interaction videos from 8 to 13 months after birth follow-up will be coded with the manual-based tool Coding Interactive Behaviour (CIB) [71] and infant development will be assessed with the Bayley Scales of Infant and Toddler Development 4th edition [72, 73]. Both assessments are conducted by trained researchers blind to group status.

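### The Research ethics section gives the safety-contact trigger in two ways: self-harm thoughts *and* EPDS ≥ 11 in the operational sentence, *or* in a later one

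*Protocol article*

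**What the plan says.** Two sentences in the protocol article, Research ethics, set out when the team contacts a mother.

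- The operational sentence opens "In case mothers indicate that they have thoughts of self-harm and experience severe depressive symptoms" and attaches a threshold in parentheses, "with Edinburgh Postnatal Depression Scale (EPDS) ≥ 11". It then says what happens: "the named postdoc researcher and psychologist on the project will contact them and, if needed, refer them to psychiatric treatment".
- Three sentences later the section states: "All participants are followed up after birth and contacted and guided if severe depression symptoms or self-harm arise".

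Two other places bear on how the trigger would work. Clinical assessments, interviews, and questionnaires describes the EPDS value of 11 as a screening threshold for the Danish population: "a cut-off of 11 or higher is the most indicative when screening for PPD". Procedure says that each week for the first six weeks after birth "mothers receive links to an online questionnaire to assess their depressive symptoms". It does not name the instrument and gives no contact rule.

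**The concern.** The two sentences join the same two conditions with different conjunctions, so they describe different groups of mothers. The narrower wording stands in the sentence that staff could act on, because only that sentence says who responds, at what score and with what next step. The article then goes straight on to conclude that the risks are justifiable, so this sentence is part of the ethical case for the trial.

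What is at stake is participant safety. Women can enter the high-risk group because of a history of severe mental illness or childhood abuse (In- and exclusion criteria). Postpartum symptoms are collected through an online link, so a response depends on a rule that is clear in advance. The article presents 11 as a screening value for PPD and gives no reason why a response to self-harm thoughts should wait for it.

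**Working it through.** No sample size, power or event figure is involved, so there is nothing to recompute. The check sets the two sentences side by side and asks which mothers each one covers.

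| | Operational sentence | Later sentence |
|---|---|---|
| Conjunction | *and* | *or* |
| Threshold | EPDS ≥ 11 | none stated |
| Who responds | postdoc/psychologist | not stated |
| Next step | referral to psychiatric treatment if needed | guidance; referral not mentioned |

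Two yes/no conditions give four kinds of mother:

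| Self-harm thoughts | EPDS ≥ 11 | Operational sentence, read literally | Later sentence |
|---|---|---|---|
| yes | yes | contact, referral if needed | contact |
| yes | no | not covered | contact |
| no | yes | not covered | contact, if EPDS ≥ 11 is what severe means there |
| no | no | not covered | no contact |

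The sentences agree in the first and last rows. They differ in the second row, and in the third if the threshold carries over.

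The second row is the core of the point. The later sentence covers this mother without a condition on her score, whereas the operational sentence gives her neither a responder nor a referral step. I read self-harm in the later sentence as including thoughts of it, which is the reading more favourable to the plan.

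The third row is less certain. The later sentence speaks of severe symptoms without a number. Carrying the value of 11 across from the operational sentence is an inference, though a natural one.

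I then looked for text that settles which sentence governs. Procedure describes the weekly questionnaires without a contact rule. Clinical assessments, interviews, and questionnaires gives the meaning of the cut-off only. Oversight and monitoring says that there is no data monitoring committee and no stopping rule, and sets no rule for contacting an individual. Nothing in the article resolves the difference.

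**The case against.** The strongest reply is that the same paragraph largely answers the point. The later sentence commits to contact for self-harm alone, for every participant. The operational sentence does not say *only if*, so the two can be read together as a combined case and a general promise. The section names one contact role, so the passive wording of the later sentence most naturally refers to the same person. On this view the *and* is loose drafting, and the detailed procedure sits in the full protocol, which is not shown.

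Much of this stands. The later sentence does suggest that *or* was meant. A reader might infer from the operational sentence that mothers with self-harm thoughts and a low score are left without contact. The article does not support that: it promises them contact, and nothing shows that anyone was missed.

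The reply does not remove the inconsistency. An article may leave a procedure to the full protocol, but this one chose to state the rule and stated it in two ways that do not match. If *or* was intended, the correction only brings the operational sentence into line with a commitment already made.

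A second tempting reading is that the article already promises contact by the psychologist for every mother with EPDS ≥ 11. It does not quite say so, because the *or* sentence sets no threshold. Such a rule would also reach beyond the self-harm gap. It could add contacts before the six-month diagnostic interview, so the sponsor should confirm it and a reviewer should not assume it.

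**Conclusion.** The point holds as an inconsistency in a stated safety rule. Read literally, the only sentence with a threshold, a responder and a referral step leaves out a mother who has self-harm thoughts and an EPDS total below 11, while a later sentence includes her. It is worth fixing because it concerns self-harm and the correction is very small.

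Its size cannot be given. The article has no figure for mothers with self-harm thoughts and EPDS below 11. Expected PPD cases would not stand in for that number, since they describe a different group.

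The conclusion rests on two assumptions: that a mother can report self-harm thoughts while scoring below 11, as the use of two separate conditions implies, and that the approved protocol, which is not shown, does not already settle the wording. If it does, only the article is at fault. A reader might also take this as a flaw in the trial's inference. It is not: sample size, the alpha level and the planned analysis are unaffected.

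**What to change.** Reword the operational sentence so that any thoughts of self-harm, regardless of the EPDS total, lead to contact by the named postdoc/psychologist and, if needed, referral to psychiatric treatment. This is the essential change.

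Separately, the sponsor should check the approved protocol and state whether EPDS ≥ 11 without self-harm thoughts also triggers contact, as the *or* sentence implies for severe symptoms.

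The cost is a short rewording and a small, unknown number of extra contacts. If the approved protocol also says *and*, the change goes to the Ethics Committee, as the article provides for any protocol change (Data entry, coding, security, and storage). If it already says *or*, only the article needs correcting.

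On the article's own timetable (Project status), the change could still have had effect. At the June 2024 revision 130 + 130 = 260 of the 292 planned women had been tested at baseline, leaving 292 − 260 = 32, and final follow-up was expected to be complete in July 2025.

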### Dissemination of results

The project will result in four articles published in peer-reviewed international scientific journals. The first article will report primary outcome findings, i.e. the effect of the intervention on PPD onset. The second article will involve secondary outcomes, including affective cognitive changes, and how these mediated effects on depressive symptoms or PPD. The remaining two articles report exploratory outcomes, including how affective cognitive performance on training tasks correlates with changes in affective cognitive outcome measures and PPD prevalence at follow-ups.

### Project status

Version 1 of the study protocol was submitted on October 23, 2023. The study was initiated in January 2023 and when the protocol was submitted, the study included 90 high-risk and 60 low-risk participants. At the revision in June 2024, 130 high-risk and 130 low-risk participants have been tested at baseline. The recruitment and treatment phase of the project is planned to take place from January 2023 to December 2024. The final follow-up is expected to be completed in July 2025.

### Oversight and monitoring

In this relatively small-scale and low-risk study, which does not involve testing a medical device, a trial steering committee was not established nor was the establishment of a Data Monitoring Committee (DMC) required. Given the relatively low-risk nature of the intervention, we decided to employ no specific stopping rules or interim analysis. The trial will proceed as planned unless unforeseen issues arise, in which case the Ethics Committee will be promptly informed, and appropriate actions will be taken to ensure participant safety.

The sponsor is an independent research fund managed by the Mental Health Services in the Capital Region of Denmark. This Research Fund had no role in the design or conduct of the study.

## Discussion

During this trial, we made several modifications to the intervention and sample size to enhance feasibility and effectiveness. These changes have only been conducted after ethical approval from the Committee on Health Research Ethics in the Capital Region of Denmark. Early in the study (December 2023), we reduced the number of intervention sessions from six to five. Some participants, residing far from the research site and nearing their due dates, faced physical limitations in travelling. To accommodate them, we allowed some sessions to be conducted online or via telephone, provided they attended at least three sessions in person. Additionally, booster sessions were made voluntary to avoid overburdening participants, thereby improving mental health outcomes and maintaining retention rates. To ensure sufficient statistical power, we increased the number of low-risk pregnant participants from 80 to 146, matching the high-risk group (March 2024). This adjustment helps balance the groups since risk status is determined only after enrollment and testing. The change from focusing our primary outcome on two measures: self-ratings of depressive symptoms and clinician-rated PPD to a single measure: clinician-determined PPD (yes/no) is currently (June 2024) under ethical review. While still assessing depressive symptom severity via self-report during the first 6 weeks postpartum, this change aims to provide a more straightforward and valid result, crucial for informing clinical practice. It also reduces the number of multiple comparisons and improves our ability to detect meaningful effects.

The results of this study will have implications for future early prophylactic interventions for pregnant women at heightened risk of PPD. Specifically, if the PACT intervention reduces the incidence of PPD, it can become a short, feasible, non-invasive prophylactic strategy for pregnant women at risk of PPD, with positive mental health implications for these women and their infants. The findings will also provide novel scientific insights into the role of affective cognitive processes for PPD risk and into how targeting these cognitive biases through advanced and tailored training may improve mental health outcomes.

## Data Availability

The de-identified data can be shared with other researchers upon reasonable request, pending approval by the Data Protection Agency.
